### Ethical Issues

This clinical trial is registered on the ClinicalTrials.gov database [NCT02796508] [72]. The UNED Ethical Review Board approved the trial. All the participants gave their written informed consent before the study started and were informed of their right to terminate participation at any time. The work described has not been published previously.

### Measurement of C-Reactive Protein in Saliva by Enzyme-Linked Immunosorbent Assay

Several parameters influencing inflammation (eg, infections, diabetes) are obtained from the participants: height and weight are recorded to obtain the body mass index (gross obesity could increase inflammation), drugs ingested (anti-inflammatories, antibiotics, antioxidants), possible infections and when they happened (last month, last week, or today), smoking habit (which may increase CRP levels in saliva), and defective oral health (eg, bleeding gums). Participants are asked not to eat or smoke at least 30 minutes before saliva collection. Following a mouth rinse with water, 1 mL of saliva is collected with a straw into a tube containing 2% ethylenediaminetetraacetic acid as preservative. Samples are stored at −80ºC until assayed. Assessment of CRP levels is performed with an enzyme-linked immunosorbent assay (ELISA) obtained from Salimetrics according to the manufacturer instructions. A saliva sample collected from participants at pretest, posttest, and follow-up assessments will be analyzed with ELISA in order to correlate the quantity of CRP with task performance.

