## Introduction

### Background

Neurocognitive frailty is the biggest threat to successful aging [1]. There is overwhelming evidence that the number of inflammatory mediators increases vastly in pathological aging [2] and in healthy aging as well [3]. This inflammation has a negative impact on cognition [4]. C-reactive protein (CRP), an acute-phase protein of hepatic origin that increases following interleukin-6 secretion by macrophages and T cells, has been identified as a hallmark of systemic inflammation, and it can be assessed by noninvasive methods in saliva [5]. A key challenge that faces the aging society is to find new approaches to understand the aging mind and brain that could enhance successful, optimal aging [6]. Another major challenge is to understand the factors that could reduce or delay the negative consequences of age-related cognitive decline [7]. The idea behind this randomized controlled trial (RCT) is that cognitive abilities could be strengthened by interventions that promote positive brain plasticity [8].

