### Objectives and Hypotheses

The study has 3 main complementary objectives:

1. To examine the behavioral and electrophysiological effects of training older adults with nonaction video games on a series of cognitive tasks designed to assess attentional functions (mainly response inhibition, distraction, and alertness) and to maintain and update verbal and visuospatial working memory. We are also interested in investigating the sustainability of the transfer effects after a 6-month no-contact period.

2. To explore whether motivation, engagement, or expectations account for possible training-related improvements.

3. To examine whether inflammatory mechanisms assessed with noninvasive measurement of CRP in saliva impair cognitive training-induced effects. Inflammatory parameters in the participants obtained by noninvasive saliva-testing methods will be analyzed in biochemical assays to study their possible correlations with cognitive abilities.

We hypothesize that participants in the Lumosity group will improve selective attention assessed with oddball and Stroop tasks and working memory assessed with Corsi blocks and *n*-back tasks in comparison with participants in the active control group. From an electrophysiological perspective, we also hypothetize that in the oddball task the cognitive video game–trained group will improve both the ability to return attention to the relevant task after having been distracted by the novel stimulus (reorientation negativity [RON]) and the ability of the brain to pay attention to the novel stimulus (P300).

Intervention studies conducted with older adults have focused mostly on training a given cognitive function and then measuring the improvement in that function [69,29] and less often on possible changes in neural activity after training [70,71]. Based on the idea that the older human brain still has some plasticity (the ability to change in response to external stimulation), our main hypothesis is that training older adults with appropriate, adapted, and motivating nonaction video games will transfer to cognitive functions that decline with age, such as attention and working memory, by improving these pillars of cognition, which are crucial to maintaining independent living and cognitive health in old age.

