### Participants

Participants were randomly assigned to 1 of the 2 parallel groups, either the intervention video game training group or the active control group (see Figure 1). The pretest, posttest, and 6-month follow-up assessments are conducted at the UNED Department of Basic Psychology II by one of the authors with the assistence of other members of the group. The training sessions were carried out at the UNED Associate Center, Escuelas Pías, Madrid, and lasted 8 to 10 weeks. A total of 138 participants were recruited from flyers, advertisements, by word of mouth, and from UNED’s special program for the elderly screened for eligibility. Finally, 75 older adults (age range 55 to 84 years) met the requirements for participation in the study and signed the consent form and were randomly assigned to the experimental or the active control groups before carrying out the laboratory tasks. The 2 groups do not differ significantly in age, years of education, global cognition, depression, memory, or verbal abilities.

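### The planned correlation of salivary CRP with task performance names no adjustment for age, so it can turn out negative with no direct CRP-cognition link

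*Protocol article*

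**What the plan says.** All references are to the protocol article.

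- The section on measurement of CRP in saliva names one analysis: the samples from the three assessments "will be analyzed with ELISA in order to correlate the quantity of CRP with task performance". Objectives and Hypotheses, under objective 3, describes the same thing: inflammatory parameters "will be analyzed in biochemical assays to study their possible correlations with cognitive abilities".
- The CRP section also states that "Several parameters influencing inflammation (eg, infections, diabetes) are obtained from the participants". Besides body mass index and drugs taken, it lists "possible infections and when they happened (last month, last week, or today), smoking habit (which may increase CRP levels in saliva), and defective oral health". It gives these variables no role in the analysis.
- General Procedure and Results add analyses of variance by group and time point and a significance level of .05. Neither mentions a covariate for CRP.
- The Background says that "the number of inflammatory mediators increases vastly in pathological aging [2] and in healthy aging as well". It goes on to describe age-related decline in working memory, executive functions and attentional control, which are the domains that the outcome tasks test.
- Participants reports that "75 older adults (age range 55 to 84 years) met the requirements for participation in the study" and that the two arms do not differ significantly in age.

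**The concern.** Objective 3 asks whether inflammation impairs cognitive gains from training, and the stated tool is a correlation between CRP and performance. On the article's own account, older participants should tend to have both more inflammation and lower scores. A correlation taken across people about 30 years apart in age (84 - 55 = 29) then picks up age as well as any effect of inflammation, and age pushes it in the hypothesised direction. The trial could report an inflammatory link to cognition that is partly or wholly an age gradient.

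Balance of age between the arms does not help. It protects a comparison of the arms, whereas this correlation is taken across individuals, and age varies just as widely within each arm.

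**Working it through.** The article gives no figure for the CRP correlation, so there is none to reproduce. The check asks how large a correlation age alone can create.

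**Inputs from the article**
- n = 75 randomised (Participants).
- n at posttest: 8 of 38 and 12 of 37 were lost (Sample Size), so 30 + 25 = 55.
- Significance level .05 (General Procedure, Results); two-sided is assumed, so the nominal rate of significant negative results is 2.5%.

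**Inputs assumed**
- The article gives the directions but not the sizes of the age correlations. The ranges used are 0.1 to 0.4 for age with CRP and -0.2 to -0.5 for age with performance.

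**Formulae**
1. With no direct link between CRP and performance, r(CRP, performance) = r(age, CRP) × r(age, performance).
2. Fisher z: m = atanh(r) × √(n - 3), and P(significant negative) = Φ(-1.96 - m).

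**Worked example at 0.3 and -0.4**
- r = 0.3 × (-0.4) = -0.12, and atanh(-0.12) = -0.1206.
- n = 75: m = -0.1206 × √72 = -1.023; Φ(-1.96 + 1.023) = Φ(-0.937) = 17.4%.
- n = 55: m = -0.1206 × √52 = -0.870; Φ(-1.96 + 0.870) = Φ(-1.090) = 13.8%.

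| r(age, CRP) | r(age, performance) | spurious r | P(significant negative), n = 75 | n = 55 |
|---|---|---|---|---|
| 0.1 | -0.2 | -0.02 | 3.7% | 3.5% |
| 0.2 | -0.3 | -0.06 | 7.4% | 6.3% |
| 0.3 | -0.4 | -0.12 | 17.4% | 13.8% |
| 0.4 | -0.5 | -0.20 | 40.5% | 30.9% |

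A simulation with 20,000 replicates per setting covered the last three rows and agrees: 7.3%, 17.9% and 41.0% at n = 75, and 6.3%, 14.1% and 31.2% at n = 55. With age partialled out, the mean correlation was about 0 and the two-sided rejection rate 4.8% to 5.5% in every age-only setting. That recovery is expected, because age is the only confounder built into those settings.

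**Infection, bleeding gums and similar artefacts** (assumed: 15% of samples with CRP raised by 2 SD)
- Unrelated to age and performance, no age effect on CRP: mean r about 0, and significant negative results stay at 2.4% to 2.6%.
- Added to age confounding at 0.3 and -0.4, n = 75: r moves from -0.12 to -0.10, and the rate falls from 17.9% to 13.4%. The artefacts dilute the spurious correlation.
- If infection also lowers performance by an assumed 0.5 SD, n = 55, no age effect: r = -0.10, and 11.5% are significantly negative. Adjusting for age leaves r at -0.10.

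**The case against.** The best defence is that the article condenses a fuller plan. Covariates, transformation and sample exclusions for a biomarker analysis are commonly left to that plan, and recording infections, drugs, smoking and oral health suggests that the authors had confounding in mind. Much of this stands. A reader might infer that the samples enter unfiltered and unadjusted by design, but the article does not say so; it is silent. What remains is that the article does name an analysis, a correlation, and its own account of aging makes the simple form of that analysis a poor choice.

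Three further inferences are tempting and are not supported.

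- *Infection, bleeding gums and anti-inflammatory drugs themselves produce a negative correlation.* Artefacts unrelated to performance pull r toward zero. Anti-inflammatory drugs would, if anything, lower CRP. Infection biases r downward only if it also lowers performance, and the article gives no figure for that.
- *Samples taken during infection must be excluded.* The Background holds that inflammation harms cognition, so illness that raises CRP and lowers scores could be part of the pathway under study. Dropping those samples changes the question toward chronic inflammation. That is a choice, so it belongs in a sensitivity analysis.
- *A moderation analysis of training gains would carry the same bias.* This has not been shown. The Introduction cites larger training effects in the older of older adults; on that evidence, age would push an association between CRP and gain upward, against the hypothesis.

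The defence is also right that CRP is in neither the primary nor the secondary outcome list, so no efficacy conclusion depends on it.

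**Conclusion.** The point holds for age. A simple correlation of CRP with performance level, taken across participants aged 55 to 84, can be negative with no direct link, in the direction that objective 3 expects. Its direction follows from the article's own statements. Its size does not: it runs from negligible at assumed age correlations of 0.1 and -0.2 to r = -0.12 at 0.3 and -0.4, with about 14% to 17% significant negative results where 2.5% is nominal. Stronger assumed correlations give more. The calculation takes roughly normal variables, one test and a two-sided .05 level.

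For the other recorded factors, the supportable statement is that they mainly add noise and bias r only if also tied to performance or age. This is a cheap improvement to a non-primary objective; it is no threat to the trial's main comparison.

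**What to change.** Replace the simple correlation with a partial correlation, or a regression of performance on CRP (preferably log CRP), adjusted for age. Add the recorded body mass index, smoking and drug use as further covariates where the sample size allows. Keep all samples in this main CRP analysis, and add a sensitivity analysis without samples reported with current or recent infection or with bleeding gums. Fix the definition of recent before CRP is linked to performance.

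The cost is small. The article puts data analysis still ahead, and the variables named here are already collected. Adjusting for age takes one degree of freedom (at n = 55, from 53 to 52), and each further single-term covariate takes one more. The sensitivity analysis has a somewhat smaller sample. It also needs infection and gum status for each sample, and the article does not say whether these are recorded anew at each visit. The primary cognitive analyses are not affected.

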**Objective:**

The main objectives of this study are (1) to evaluate the effects of a randomized computer-based intervention consisting of training older adults with nonaction video games on brain and cognitive functions that decline with age, including attention and spatial working memory, using behavioral measures and electrophysiological recordings (event-related potentials [ERPs]) just after training and after a 6-month no-contact period; (2) to explore whether motivation, engagement, or expectations might account for possible training-related improvements; and (3) to examine whether inflammatory mechanisms assessed with noninvasive measurement of C-reactive protein in saliva impair cognitive training-induced effects. A better understanding of these mechanisms could elucidate pathways that could be targeted in the future by either behavioral or neuropsychological interventions.

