
### General Procedure

Participants in the study were randomly assigned to the cognitive nonaction video game training group or the noncognitive game training active control group. The introduction of an active control group is necessary to avoid placebo effects [54]. Based on the results of our meta-analytic study [61], we use training regimes that are not too long to avoid loss of motivation, and simple, nonaction games that appeal more to elders. According to the temporal discount hypothesis [85], future rewards are less valuable than inmediate rewards. In each session, the trainees play 10 nonaction video games from Lumosity, described below.

The main question examined in our study is whether group (experimental group, active control group) interacts with testing session (pretest, posttest, and follow-up) with regard to performance on a series of cognitive tasks. At least 2 measures for each cognitive domain are acquired to examine transfer of training to untrained tasks demanding attention and working memory. We selected these cognitive domains because these functions deteriorate with aging and tax functions that are critical for independent living. To explore the underlying neural mechanisms of successful transfer of training gains to attentional mechanisms (alert, distraction, and inhibitory effects) and executive control (spatial working memory), electrophysiological data (ERPs) are recorded at pretraining (T1), posttraining (T2), and 6-month follow-up (T3).

All the methodological designs of the primary outcome measures have been constructed using the rules of counterbalancing and stimulus rotation. Response keys are counterbalanced across conditions. The computerized tasks have been programmed using E-Prime 2.0 (Psychology Software Tools Inc). All the statistical analyses of the behavioral results will be performed using SPSS (IBM Corp) and results will be considered significant at *P*<.05, with Bonferroni-corrected post hoc tests performed as appropriate. Continuous EEG activity are recorded in our laboratory with thin electrodes from 34 scalp sites using a NuAmps amplifier as mentioned before.

After randomization and initial assessment (baseline), participants were invited to attend the University Center of Escuelas Pias in Madrid to perform the training sessions in small groups. Trained and active control groups followed 16 training sessions carried out on different hours and days that lasted approximately 10 to 12 weeks.

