## Results

All analyses will be performed with the SPSS (IBM Corp) program. Statistical significance is considered as a *P* value of <.05. Analyses of variance will be conducted with 2 groups (experimental and active control) at 3 time points (pretest [baseline], posttest [postintervention], and follow-up [after 6 months without contact]). Electrophysiological data will be analyzed using EEGLAB/ERPLAB.

The preparatory phase for using the games has been completed. License to use the games has been granted by Lumosity. Participants have been recruited, pretested, and trained. The final results from this RCT are expected by the end of 2017.

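### Objective 3 asks whether inflammation weakens the training effect, but the only CRP analysis the article names is a correlation with performance, which contains no training contrast

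*Protocol article*

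**What the plan says.** Objective 3, under Objectives and Hypotheses, is "To examine whether inflammatory mechanisms assessed with noninvasive measurement of CRP in saliva impair cognitive training-induced effects"; the abstract's Objective paragraph says the same. The next sentence of Objective 3 gives the use of the assays: "to study their possible correlations with cognitive abilities". The section on measuring CRP in saliva sets the sampling times ("A saliva sample collected from participants at pretest, posttest, and follow-up assessments will be analyzed with ELISA") and gives the purpose as "in order to correlate the quantity of CRP with task performance". It also records factors that affect inflammation: "Several parameters influencing inflammation (eg, infections, diabetes) are obtained from the participants".

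On what counts as a training effect, General Procedure puts the main question as "whether group (experimental group, active control group) interacts with testing session (pretest, posttest, and follow-up", and the Oddball Task section predicts a group × session interaction. The analysis text under Results reads "Analyses of variance will be conducted with 2 groups (experimental and active control) at 3 time points". It has no CRP term.

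**The concern.** If a training effect is a group × session interaction, then impairment of it by inflammation means that this interaction varies with CRP. Both places that say how CRP will be used name a correlation with a level of cognition or task performance. Neither mentions group, change from pretest, or moderation.

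A correlation of that kind shows whether people with higher CRP perform differently. It could be found at pretest, before anyone has trained. At stake is whether one of three named main objectives can be answered by the analysis attached to it. There is also a risk that a CRP–performance correlation, or its absence, is later taken as evidence about training.

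**Working it through.** The article gives no figure for the CRP analysis, so there is none to reproduce. The check is algebra first, then illustrations of size.

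**Inputs from the article (Sample Size; Results).** Assigned: 38 + 37 = 75. Left at posttest: 38 − 8 = 30 experimental and 37 − 12 = 25 control, 55 in all. Significance level .05, taken here as two-sided.

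**Assumptions.** All CRP effect sizes and the pre–post correlations. All 75 are assumed to have a pretest CRP value, and all 55 to have CRP and posttest scores.

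**Step 1: what each analysis estimates.** Write posttest performance as Y = a + βC + τG + δGC + error, with C the standardised pretest CRP and G = 1 for the experimental group. Objective 3 asks about δ. A correlation of C with Y, arms pooled, reflects the slope β + pδ, where p = 30/55 = 0.545. It mixes β, which has nothing to do with training, with δ.

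**Step 2: put numbers in.**
- β = −0.4, δ = 0: pooled slope −0.4. There is a correlation but no impairment of training.
- β = +0.25, δ = −0.5: pooled slope 0.25 − 0.545 × 0.5 = −0.02. Training is impaired but there is almost no correlation.
- β = 0, δ = −0.5: pooled slope −0.27. There is a correlation, but it looks like a weaker version of the first case.

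**Step 3: simulation.** 4,000 runs per row, 30 and 25 participants, residual SD 0.8 given pretest (pre–post correlation about 0.6 before CRP and group effects). The stated analysis is taken as a Pearson correlation of CRP with posttest score, arms pooled. The comparison is a CRP × group term in a model of posttest adjusted for pretest.

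| Scenario | Mean r | Correlation significant | CRP × group significant |
|---|---|---|---|
| β = −0.4, δ = 0 | −0.37 | 82% | 5% |
| β = +0.25, δ = −0.5 | −0.02 | 6% | 57% |
| β = 0, δ = −0.5 | −0.25 | 45% | 57% |
| β = 0, δ = 0 | 0.00 | 5% | 5% |

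**Step 4: a correlation at pretest alone.** By Fisher's z, power = Φ(atanh(r) × √(75 − 3) − 1.96).
- r = 0.2: Φ(0.203 × 8.49 − 1.96) = 41%
- r = 0.3: Φ(0.310 × 8.49 − 1.96) = 75%
- r = 0.4: Φ(0.424 × 8.49 − 1.96) = 95%

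These are chances of finding an assumed correlation before any training has taken place.

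**Step 5: what the direct test can detect.** The standard error of δ is about √(1 − ρ²) × 2/√55, with ρ the pre–post correlation.
- ρ = 0.7: 0.714 × 0.270 = 0.19; times 2.8 (1.96 + 0.84) gives 0.54
- ρ = 0.5: 0.866 × 0.270 = 0.23; times 2.8 gives 0.65

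So 80% power needs a change in the training effect of about 0.54–0.65 SD per SD of CRP. The approximation is slightly generous. At ρ = 0.6 and δ = −0.5 the standard error is 0.8 × 0.270 = 0.216, and the formula gives Φ(0.5/0.216 − 1.96) = 64%, against 57% simulated.

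**The case against.** The strongest reply is that the words about correlation are a purpose clause at the end of an assay paragraph in a condensed article. The article does not say that correlation is the only CRP analysis, and a statistical analysis plan that is not shown could hold a moderation model. Nor does it say that the correlation is taken visit by visit, on raw scores, or with the arms pooled. Correlating CRP with change, separately by arm, would fit the same words and come closer to the objective. The pooling in the simulation is a choice made for illustration. Objective 3 also contains the weaker correlational aim, and the Introduction says that the study explores these mechanisms.

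Most of this stands as a limit on the point, but it does not remove it. The article names a method for a main objective twice, and both times the method as written lacks the group and change contrast that the objective needs. Where the authors want an interaction, they say so. A plan that added a moderation term would be going beyond the published text, which would still need aligning.

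Three stronger readings should be resisted.
- A reader might infer that the trial will report a CRP correlation as proof of impaired training. The article states no such intention; it is a risk.
- A reader might count it as a fault that the recorded inflammation factors are not tied to an analysis. Covariate lists are commonly left to the analysis plan.
- A reader might object that posttest and follow-up CRP are measured after randomisation. That matters only if those values are used as modifiers, and the article does not say they are.

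**Conclusion.** The point holds as a mismatch between a stated objective and the analysis stated for it. Objective 3 concerns modification of the training effect; a correlation of CRP with cognitive abilities or task performance does not estimate that. This follows from the article's own treatment of a training effect and needs no assumed effect size.

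The percentages are illustrative. They rest on assumed CRP–performance relations, assumed pre–post correlations of 0.5–0.7, and complete CRP data on the 75 or 55 participants. The 6% figure depends on an assumed offsetting main effect.

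Severity is minor to moderate. CRP appears in neither the primary nor the secondary outcomes, and the main group × session question is untouched.

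**What to change.** State that Objective 3 is assessed by a pretest log-CRP × group term in the model of posttest performance adjusted for pretest, and likewise for follow-up; or, in repeated-measures form, by pretest CRP × group × session. Report the slope and its 95% confidence interval as exploratory. Describe simple CRP–performance correlations as descriptive only.

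Use at most a small prespecified set of the inflammation factors already recorded, as covariates or in a sensitivity analysis. A long list is hard to support with 55 completers, and main-effect covariates alone do not remove confounding of an interaction. Adjusting for factors such as body mass index may also take out part of the inflammation of interest.

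Alternatively, reword Objective 3 as an association between CRP and cognition, which the stated correlation can address.

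The cost is wording only; the data are already being collected. The downside of the first option is a wide interval, so a non-significant interaction could not be read as showing that inflammation makes no difference.
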